#### **86**    Obtaining nasopharyngeal samples

A single paediatric Copan flocked nasopharyngeal swab will be obtained from children at the time points specified in the schedule of events. Detailed practical instructions regarding the collection of NPS will be outlined in the relevant study specific procedure.

Once obtained, NPS will immediately be placed aseptically into a vial of RNaProtect® cell reagent, the swab snapped as per manufacturer's recommendations and the lid of the vial closed immediately.

#### **87**    Obtaining oral swabs

A saliva sample collected using an Oracol swab will be obtained from children at the time points specified in the schedule of events. Detailed practical instructions regarding the collection of Oracol swabs will be outlined in the relevant study specific procedure.

Once obtained, the swab will immediately be placed in the collection tube according to the manufacturer's instructions.

#### **88**    Additional clinical samples

Any additional blood or other samples (e.g. urine) required for the routine clinical assessment and care of an infant may be obtained as indicated with the verbal consent of the parent/guardian.

#### **89**    Sample transport

Samples will be transported from the Health Centre field site to the main MRC site laboratories at Fajara as follows:

## **90 Blood samples**

Blood samples will be transported in cool boxes although must not be frozen. Samples must reach laboratory within 3 hours allowing serum separation to take place within 4 hours. Non-serum samples must reach the laboratory within the same timeframe. All samples will be processed in the research immunology laboratory according to study specific procedures.

## **91 Nasopharyngeal swabs**

NPS vials will be placed on an ice block and transported to the laboratory within 3 hours for processing and storage within 4 hours. Samples will be processed in the research immunology laboratory according to study specific procedures, with the 1ml sample being split into five equal aliquots of 200ul and stored at -70 °C.

## **92 Oral swabs**

Oral swabs will be placed in a cool box and transported to the laboratory within 3 hours for processing and storage within 4 hours. Samples will be processed in the research immunology laboratory according to study specific procedures. Samples will be diluted 1:2 in buffer according to protocols developed at Public Health England Laboratories and stored at -70 °C until further use.

## **93 Endpoint evaluations**

### **94 Laboratory endpoints**

## **95 Nasopharyngeal microbiome sequencing**

Microbiome sequencing will be performed via collaboration with [name] (University of Edinburgh, UK and University Medical Centre, Utrecht). NPS samples will be shipped frozen on dry ice to either the University of Edinburgh or Utrecht Medical Centre [name] laboratory (to be confirmed). DNA will be extracted from NPS collected material using phenol/bead beating in combination with the AGOWA Mag mini DNA extraction kit. Microbiota will be studied by Illumina Miseq sequencing of the 16S small subunit ribosomal DNA gene according to previously described methods by the [name] group [69]. After DNA isolation, the V4 region of the 16S-rDNA gene will be amplified by qPCR, fragments pooled and the library sequenced. Specific PCR for *S. pneumoniae* and *S. aureus* may be performed to validate any longitudinal changes in these species suggested by 16s fragment analysis.

## **96 Peripheral blood and nasopharyngeal transcriptomic studies**

RNA will be extracted from whole blood in Paxgene® tubes and NPS collected material according to protocols optimized in the [name] laboratory (University of Edinburgh) and [name] laboratory respectively. Extracted RNA will be shipped frozen on dry ice to the University of Edinburgh and microarrays performed on the Affymetrix® platform. Key signatures identified will be validated further by gene-specific RT-PCR in the first instance.

## **97 Influenza-specific IgA and IgG**

An aliquot of NPS collected material and oral fluid will be shipped frozen on dry ice to RIVM laboratories in the Netherlands, where anti-influenza IgA will be measured using a protein microarray [70]. This fluorescence-based assay utilizes very small amounts of material and preliminary data shows very good correlation with nasal fluid anti-influenza IgA estimated by more traditional indirect enzyme-linked immunosorbent assay (ELISA) methods ([name],

[name], unpublished). In addition, indirect ELISA assays to determine anti-influenza IgA and IgG from oral fluid, where more material is available will be set up and performed at the MRC Gambia immunology research laboratory. Total IgA and IgG will also be estimated in NPS material and oral fluid (by ELISA) and influenza-specific IgA and IgG expressed as a ratio of total IgA and IgG respectively. Further exploratory assays may be carried out after optimization to obtain a more functional output of anti-influenza activity in mucosal secretions.

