## 17 Study endpoints

### 18 Primary endpoints

- Influenza-specific nasal IgA responses at day 21 post-LAIV
- Oral fluid IgA and IgG responses at day 21 post-LAIV
- Gene expression changes in nasal and systemic samples at day 2 following LAIV
- Nasopharyngeal microbiome profiles at baseline, day 7 and day 21 following LAIV
- Density of *S. pneumoniae* before and after LAIV as established by quantitative polymerase chain reaction (PCR)

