## 20 Study design

### 21 Type of study and design

All primary objectives and most exploratory objectives will be addressed through the conduct of a phase 4, randomized, controlled clinical vaccine trial. A total of 330 healthy children aged 24 – 59 months will be enrolled into one of three groups of equal size (3 x 110 children):

- (i) LAIV-vaccinated (Group A - blood sample at day 0, 2, 21)
- (ii) LAIV-vaccinated (Group B - blood sample at day 0, 7, 21)
- (iii) Control group (Group C)

Allocation concealment will be maintained from the start through the use of sealed envelopes. Block randomization stratified by sex will be used and a randomization sequence will be generated by an MRC Statistician not involved in the study. Investigators will not be blinded to group allocation from this point onwards as the sampling schedule differs between groups. Local laboratory staff will therefore not be blinded for this reason, but samples sent to external laboratories will be blinded (see section 3.2.3).

Two LAIV-vaccinated groups are included in order to achieve several exploratory objectives, which require blood sampling at different time points following vaccination, whilst minimizing the number of times children are bled times (i.e. 2nd blood sample at either day 3 or day 7 post-LAIV, but not both). The unvaccinated subjects will serve as a control group for the primary objective of assessing the impact of LAIV on the nasopharyngeal microbiome. Section 8 details the statistical considerations made to decide on the sample sizes to be recruited. The vaccination and sampling schedules for groups A, B and C are detailed in Tables 1.

Group C subjects will be administered LAIV after the NPS is taken on their day 21 visit, to offer them the same level of protection against influenza illness by participating in the study as those in groups A, B and D.

An additional 35 healthy children aged 24 – 59 months will be recruited in the 2nd phase of recruitment (Jan – June 2018) to assess the objective of how modulation of the nasopharyngeal microbiome with antibiotics impacts the mucosal immunogenicity to LAIV

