## 25 Blinding of external laboratories undertaking analyses

Allocation concealment will be maintained as detailed above in section 3.2.1. Laboratory personnel processing samples and performing flow cytometry analyses on blood samples at the MRC Gambia will not be blinded to group allocation as sampling schedules vary across the groups (Tables 1 – 3). Laboratory personnel in external laboratories assessing the nasal and oral IgA, as well as serum HI, immunological endpoints will be blinded to group allocation, as well as whether samples are pre or post vaccine by allocation of a sample number. The code matching these sample numbers, to subject identification number and visit number will be held by investigators at the MRC Gambia.

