### **148**    Influenza-specific and total IgA and IgG (ELISA)

Standard operating procedures for ELISAs to measure influenza-specific and total IgA and IgG from nasal/oral fluid will be established at the MRC Gambia immunology research laboratories. These will be based on well-established and QC'd procedures currently being used in line with Good Clinical Laboratory Practice (GCLP) at the mucosal immunology laboratory at Imperial College London. QC and QA procedures will be established for local protocols.

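### Oral-fluid IgG has no blinded component and the mucosal IgA ratios are only partly blind, because their ELISAs run in the local laboratory, which the plan leaves unblinded

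*Combined protocol and SAP*

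**What the plan says.** **Endpoints.** Section 18 lists two mucosal antibody endpoints as primary: "Influenza-specific nasal IgA responses at day 21 post-LAIV" and "Oral fluid IgA and IgG responses at day 21 post-LAIV".

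**External blinding.** Section 25 states: "Laboratory personnel in external laboratories assessing the nasal and oral IgA, as well as serum HI, immunological endpoints will be blinded to group allocation". The masking also covers visit: "as well as whether samples are pre or post vaccine by allocation of a sample number".

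**Local blinding.** Section 21 gives the differing sampling schedules as its reason and states: "Local laboratory staff will therefore not be blinded for this reason, but samples sent to external laboratories will be blinded". Section 25 repeats that reason but names only sample processing and flow cytometry on blood as unblinded local work. It does not mention ELISA. Section 24 adds the letter A, B, C or D to the subject number once the child is allocated, and that number then identifies the laboratory samples.

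**Where the assays run.** Section 97 sends swab material and oral fluid to an external laboratory for anti-influenza IgA by protein microarray. Oral-fluid anti-influenza IgA and IgG are also measured by ELISA, "where more material is available will be set up and performed at the MRC Gambia immunology research laboratory". Section 97 adds total IgA and IgG by ELISA in both fluids and expresses the specific antibody as a ratio to the total, but does not name the site of the total assays. Section 148 does: "ELISAs to measure influenza-specific and total IgA and IgG from nasal/oral fluid will be established at the MRC Gambia".

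**The concern.** Read alone, section 25 suggests that the mucosal antibody results come from laboratories that know neither the group nor the visit. Sections 97 and 148 show that part of each result is produced elsewhere, by staff whom section 21 leaves unblinded. Running an ELISA involves judgement on dilution, repeat runs and acceptance of the standard curve. These particular assays are still to be set up locally, whereas section 147 describes the external microarray procedures as already established.

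Two results are most exposed. One is oral-fluid IgG, which has no blinded measurement anywhere in the plan. The other is exploratory objective (iv), which compares mucosal response between Group D (azithromycin, then vaccine) and matched vaccinees. Section 21 protects that comparison at the matching step, by using someone who does not know the immunogenicity data. It does not protect it at the local ELISA bench, where part of the outcome is measured.

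**Working it through.** There is no sample size, power or error rate to reproduce. The check is who measures each component and what they can know.

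**Step 1. Components of each ratio** (sections 97, 147 and 148 for the site; sections 21 and 25 for blinding)

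| Result | Numerator | Denominator | Blinded components |
|---|---|---|---|
| Nasal IgA / total IgA | External microarray, blinded | Local ELISA, not blinded | 1 of 2 |
| Oral IgA / total IgA, microarray | External microarray, blinded | Local ELISA, not blinded | 1 of 2 |
| Oral IgA / total IgA, additional ELISA | Local ELISA, not blinded | Local ELISA, not blinded | 0 of 2 |
| Oral IgG / total IgG | Local ELISA, not blinded | Local ELISA, not blinded | 0 of 2 |

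No ratio is blinded in both parts.

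**Step 2. What the local bench can know.** Group: yes, by the general statement in section 21 and the suffix in section 24. Visit: this is an inference. Pre/post masking is described only for external laboratories, but no section says that the local ELISA tubes display the visit.

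**Step 3. Does the stated reason reach these assays?** Differing schedules do make it hard to blind fresh-blood flow cytometry (section 99). Swab and oral-fluid material is stored at -70 °C (sections 91 and 92), so it can be recoded before assay whatever the schedule.

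**Step 4. How an error would travel.** Let k be a multiplicative error in a child's measured fold rise.

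- *Objective (i), extremes of response.* If k is the same for all vaccinees, observed rise = k × true rise. The ranking is unchanged, so the same 30 children fall at each end (section 121). Correlations with log rise are unchanged too, because log k is a constant.
- *Objective (ii), responders versus non-responders.* If the 2-fold rule uses the ratio, then observed rise ≥ 2 means true rise ≥ 2/k. Some children change class, but the documents give no route by which this could depend on their microbiome, which is sequenced elsewhere (section 95). That is non-differential misclassification.
- *Exploratory objective (iv).* If k differs between Group D and the matched children, the difference in mean log rise is biased by log k(D) - log k(matched). This goes straight into the estimated antibiotic effect.
- *Oral IgG.* A k other than 1 changes the size of the reported rise, with no blinded measurement to set against it.

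**Step 5. Tubes involved.** Vaccinees: 110 + 110 + 35 = 255, the figure also given in section 101. Aliquots: 255 × 2 visits (day 0 and day 21) × 2 fluids = 1,020 at planned enrolment.

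**The case against.** The strongest reply is that nothing is hidden and little of primary importance is touched.

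- The plan promises blinding to external laboratories only and says openly that local staff are unblinded. A reader might infer a broken promise that all IgA laboratories are blinded. The documents do not support that. **This stands.**
- Influenza-specific IgA has a blinded microarray measurement in both fluids, and the local oral IgA ELISA is additional. A reader might infer that the primary IgA endpoints are unblinded. They are partly blind. If the 2-fold rule is applied to the microarray value itself, which sections 122 and 125 leave open, the nasal responder call is fully blind. **This stands.**
- Objectives (i) and (ii) are associations among vaccinees. The letters A and B distinguish only blood-sampling times and say nothing about expected IgA. Group C gives no oral swabs, and its nasopharyngeal swabs are listed for sequencing. **This stands**, and it is why the point bears mainly on Group D.
- Oral IgG serves exploratory objective (xii), and no planned analysis in sections 125 to 130 names it. **This stands in part.** Section 18 still lists it as a primary endpoint, and it is the result with no blinding at all.
- Tube coding may be settled in the laboratory analytical plan required by section 144, which is not available here. **This stands as a caveat.** If so, sections 21 and 25 need only be brought into line with it. As written, section 21 is a stated rule of no local blinding, not an omitted detail.

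**Conclusion.** The gap is real but narrower than it first appears. It is complete for oral-fluid IgG, partial for the nasal and microarray-based oral IgA ratios, and most consequential for the Group D versus matched-control comparison. For primary objectives (i) and (ii) the likely effect is limited to non-differential misclassification. That conclusion assumes that any visit-related error is roughly uniform across vaccinees and that the bench does not know microbiome or expression results.

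No size can be given. It is tempting to turn an assumed reading error into a shift in the responder rate. The documents supply neither a plausible error nor a standard deviation of the fold rise, and do not say whether the 2-fold rule uses the ratio. The responder rate is also not itself a listed endpoint. ELISA is read by instrument, so any bias may well be modest. The case for change rests on the plan's own choice to mask group and visit for these antibody measurements, and on the low cost of extending it.

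**What to change.** 1. Extend the section 25 recoding to all swab and oral-fluid aliquots assayed by ELISA at the local laboratory: sample number only, with no group suffix and no visit.
2. Section 25 leaves the code with local investigators. Specify that it is kept by someone who does not work on the ELISA bench.
3. Run both visits of a child on the same plate, in random well order.
4. Amend sections 21 and 25 so that only sample processing and fresh-blood flow cytometry are listed as unblinded local work.

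The cost is relabelling about 1,020 stored aliquots at planned enrolment, and a change of wording. No extra children, visits or samples are needed.

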## **98 Serum haemagglutination inhibition assays**

Serum aliquots will be shipped frozen on dry ice to Public Health England laboratories, Colindale, UK and/or The University of Edinburgh and serum antibody titres measured against the three influenza strains included in the vaccine.

## **99 Flow cytometry assays**

Fresh whole anti-coagulated blood will be used for optimized exploratory flow cytometry assays at several times points to assess innate cell phenotyping, influenza-specific T-cell responses, B-cell phenotyping and peripheral T-follicular helper cells following LAIV (Table 3). Influenza-specific T-cell responses will be assessed by intra-cellular cytokine staining following stimulation with overlapping peptide sets matching conserved internal proteins (matrix and nucleoprotein) and HA of the influenza A vaccine strains. All these assays will be performed at the MRC Unit The Gambia research immunology laboratory.

## **100 Viral RNA detection**

An aliquot of NPS collected material will be used to extract viral RNA at the MRC Unit The Gambia molecular laboratories. The presence of several respiratory viruses at vaccination (e.g. parainfluenza, adenovirus, coronavirus, rhinovirus) will be evaluated by viral multiplex rRT-PCR. Shedding of LAIV strains (pdmH1N1, H3N2 and influenza B) will be assessed at day 2 and 7 post-LAIV (Table 3).

## **101 IFITM3 gene polymorphisms**

Genomic DNA will be extracted from an aliquot of whole blood (Table 3). DNA will be shipped frozen on dry ice to [name] laboratory in Oxford, who will perform genotyping of the IFITM3 rs12252 gene of all vaccinated subjects (n = 255) in the study for exploratory analyses to see whether polymorphisms in IFITM3-rs12252 impact on immunogenicity of LAIV. IFITM3 CC genotype is associated with greater expression of interferon-stimulated genes in wild-type pdmH1N1 infections and the 1000 genome project suggests a relatively high prevalence of this genotype in the Gambia at 21% ([name], personal communication). It is possible, therefore, that different innate immune responses to LAIV due to IFITM3 polymorphisms may account for differences in downstream adaptive immune responses.

## **102 Safety considerations**

### **103 Definitions**

#### **104 Adverse event**

An adverse event (AE) is any untoward medical occurrence in a child enrolled in the study which does not necessarily have a causal relationship with the either the vaccine or drug administered or study participation. An adverse event therefore includes any unfavorable and unintended sign (including an abnormal laboratory finding), symptom or disease occurring

during the study.

Any AE which occurs after an immunization may be termed an AE following immunization (AEFI).

### **105 Serious adverse event**

An AE will be considered serious (i.e. an SAE) if:

- It results in death
- Is life-threatening
- Requires inpatient hospitalization
- Results in persistent or significant disability/incapacity

 This refers to an event when the child was at risk of death at the time of the event; it does not refer to an event which hypothetically might have caused death if it were more severe

The start date for an SAE is defined as the day the relevant SAE criteria (as above) was met and not the day an AE which subsequently developed into an SAE began. The end date for an SAE is the day the criteria rendering the SAE serious resolves, i.e. the end of the hospitalization period or the time the SAE was no longer considered life-threatening. In these cases the related AE may be ongoing after the end of the SAE (e.g. if a child has ongoing pneumonia but is discharged from hospital). 'Death' and 'Persistent or significant disability/incapacity' will be defined as ongoing and will be closed for the purposes of further reporting once relevant clinical details have been captured (e.g. cause of death) and, in the case of disability/incapacity, the condition is considered stable in the short term.

All SAEs occurring throughout the study must be reviewed and evaluated by a study clinician (SAE relationship to study vaccine must be evaluated as outlined in Section 7.1.4) and recorded on an SAE form and reported. All such SAEs should also be followed until satisfactory resolution or until the investigator deems the event to be chronic or the patient to be stable.

### **106 Assessment of severity**

All AE will be graded for severity using the terms mild, moderate and severe. The event itself, however, may be of relatively minor medical significance (such as a severe headache). This is not the same as 'serious', which is based on the outcome or action required (see section 7.1.2 above).

The following terms are used to define severity:

**Mild (Grade 1):** Mild signs or symptoms which appear to be no more than a minor irritation. Symptoms do not require therapy or a medical evaluation; signs and symptoms are transient. Little or no change in normal activities (e.g. feeding, sleeping, behavior etc); minimal parent/guardian concern.

**Moderate (Grade 2):** Events introduce some inconvenience or concern to the parent/guardian. Usually improved by simple therapeutic measures (e.g. paracetamol). Moderate change in normal activities (e.g. feeding, sleeping, behavior etc); moderate parent/guardian concern.

**Severe (Grade 3):** Events significantly alter the child's normal daily activities (feeding, sleeping, behavior, etc) and generally require systemic drug therapy or other treatment; high parent/guardian concern.

The following specific AEs will be graded according to the following parameters:

**Measured fever will be graded as follows:**

1. Mild: measured temperature from 38.0°C to 38.4°C axillary
2. Moderate: measured temperature from 38.5°C to 39.0°C axillary
3. Severe: measured temperature >39.0°C axillary

**Tachypnea will be graded as follows:**

1. Mild: measured respiratory rate 31 to 40 breaths/min
2. Moderate: measured respiratory rate 41 to 50 breaths/min
3. Severe: measured respiratory rate 51 breaths/min or greater

**7.1.4 Assessment of relatedness**

The clinician's assessment of an AE's relationship to the vaccine or drug is part of the documentation process, but it is not a factor in determining what is or is not recorded in the study. If there is any doubt as to whether a clinical observation is an AE, the event should be recorded. All AEs must have their relationship to study vaccines assessed using the terms: related or unrelated. To help assess, the following guidelines will be used:

- Related – The event is temporally related to the administration of the study vaccine or drug **and** no other etiology explains the event.
- Not Related – The event is temporally independent of study vaccine or drug and/or the event appears to be explained by another etiology.

Solicited local and systemic AEs occurring in the week following vaccination with Nasovac-S will, in most cases, be considered to be related to the study vaccine in the absence of a clear alternative diagnosis (e.g. malaria, lower respiratory tract infection). Details of expected AEs in the Summary of Product Characteristics will be used to aid this decision.

Any AE which is judged to be related to the study vaccine will be defined as a suspected adverse reaction (SAR).

Any SAE which is judged to be related to the study vaccine but unexpected will be defined as a suspected unexpected serious adverse reaction (SUSAR).

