**107 Methods and timing for assessing, recording, and analyzing safety parameters**

As the safety profiles of both interventions (Nasovac-S and azithromycin) are well established and the study does not have defined safety endpoints, data on adverse events will be collected by passive follow up and questions asked during scheduled visits to the clinical trial site.

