**108 Time windows for the collection of adverse event data**

All adverse events that occur through day 21 post-vaccination with Nasovac-S in groups A, B and D will be assessed and recorded (during scheduled visits at day 2, 7 and 21 after vaccination or if subjects present to the clinical trial site due to illness in between these visits). All adverse events occurring through Day 28 following administration of azithromycin (Group

D only) will be assessed and recorded (at the scheduled visit at day 28 after azithromycin or if subjects present to the clinical trial site due to illness before this visit). Parents/guardians will be advised to contact the study team via telephone or attend the clinical trial site if their child is unwell in between scheduled study visits.

Group C will receive Nasovac-S after NPS has been taken on the day 21 visit, so they are also afforded the same potential benefit of influenza vaccination by participating in the study as groups A, B and D. Given the existing safety data on Nasovac-S (Section 4.1.9), no extra visits will be scheduled for group C specifically for the purpose of gathering adverse event data. Parents/guardians will, however, be advised to contact the study team or bring their child to the health centre if they have any concerns and adverse event data collected, graded and investigated as per AEs in other groups detailed in this section. This will be particularly relevant for post-vaccine AEs for 7 days following vaccination, but aligns with the agreement to assess all study subjects if they are unwell until October 31st of the year of vaccination.

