#### **111 Unsolicited safety data collection**

All AE will be classified according to their seriousness (section 7.1.2), severity (section 7.1.3) and relatedness to vaccination or azithromycin (section 7.1.4).

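### The SUSAR definition names only the vaccine, so read literally a serious unexpected azithromycin reaction in Group D does not trigger the trial's only automatic recruitment pause

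*Combined protocol and SAP*

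**What the plan says.** Several sections treat azithromycin as a study intervention:

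- The adverse event definition (heading 104) refers to "a causal relationship with the either the vaccine or drug administered or study participation".
- The guideline for a related event in section 7.1.4 reads "The event is temporally related to the administration of the study vaccine or drug".
- Heading 107 begins "As the safety profiles of both interventions (Nasovac-S and azithromycin) are well established".
- Heading 108 provides for collecting "All adverse events occurring through Day 28 following administration of azithromycin" in Group D.
- Heading 111 has unsolicited events classified for "relatedness to vaccination or azithromycin (section 7.1.4)".
- Heading 156, Risks, names the product characteristics of both agents as the reference for expected events.

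The operative wording is narrower. Heading 105 says "SAE relationship to study vaccine must be evaluated as outlined in Section 7.1.4". Section 7.1.4 says "All AEs must have their relationship to study vaccines assessed using the terms: related or unrelated". It then defines a SAR by relation to the study vaccine, and a SUSAR likewise: "Any SAE which is judged to be related to the study vaccine but unexpected will be defined as a suspected unexpected serious adverse reaction".

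Safety reporting procedures (heading 115) twice describes a SUSAR by relation to the *study product*, a term the protocol does not define. Pause rules (heading 117) makes any SUSAR an automatic pause in recruitment and gives no other automatic trigger.

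**The concern.** A definition that feeds a stopping rule has to cover every agent the trial gives. Here it covers one of two. Group D takes azithromycin 28 days before the vaccine, so there is a period in which azithromycin is the only study agent a child has received. A serious, unexpected reaction in that period is the kind of event a pause rule exists for, yet the definition as written leaves it out.

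What is at stake is whether the pause is automatic. The children are healthy, and the protocol's own account of benefits (heading 157) accepts that they have no clinical need for the antibiotic. For such a group the response to a serious unexpected reaction should not depend on which of two sections the reader consults.

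**Working it through.** The plan gives no figure to reproduce, and the check is mainly one of wording.

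**Step 1. Which agents does each rule cover?**

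| Place | Agent covered |
|---|---|
| Adverse event definition (104) | vaccine or drug |
| SAE relatedness instruction (105) | vaccine only |
| Relatedness instruction for all AEs (7.1.4) | vaccine only |
| Guideline for a related event (7.1.4) | vaccine or drug |
| SAR and SUSAR definitions (7.1.4) | vaccine only |
| Classification of unsolicited AEs (111) | vaccination or azithromycin |
| SUSAR report to the ethics committee (115) | *study product*, undefined |
| SUSAR report to the vaccine manufacturer (115) | *study product*, undefined |
| Regulator's 7- and 15-day deadlines (115) | any SUSAR, not described further |
| Automatic pause (117) | any SUSAR, not described further |

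Section 7.1.4 disagrees with itself: its guideline covers both agents and its definitions cover one. No sentence says that an azithromycin reaction counts as a SUSAR.

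**Step 2. Apply the rules to one event.** Take a serious, unexpected event attributed to azithromycin in Group D between day -28 and day 0.

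- *By the section 7.1.4 definition.* The vaccine has not been given, so the event cannot be related to it. It is not a SUSAR, and the automatic pause does not follow.
- *By the heading 115 wording, if* study product *includes azithromycin.* The event is a SUSAR. The pause follows, and so do the deadlines of 7 days (fatal or life-threatening) and 15 days (other).

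The wording under heading 115 does not settle which reading is right. One of its two uses of *study product* concerns reports to the Serum Institute of India, which makes the vaccine. Azithromycin is made by another company (heading 44).

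**Step 3. Who is affected?**

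- Group D is 35 of 330 + 35 = 365 planned children: 35/365 = 9.6%.
- Active participation in Group D is 49 days. Azithromycin is the only study agent received for the first 28 of them: 28/49 = 57%. The +7-day window for the day 0 visit in Table 2 can extend this to 28 + 7 = 35 days. These are shares of calendar time, not of risk.
- Group D is recruited after groups A, B and C are complete (heading 23), so a pause at that stage would hold up Group D only.

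The documents give no rate for serious unexpected azithromycin reactions, so no expected number of events can be stated.

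**The case against.** The strongest reply is that the intent is plain. The related-event guideline, the classification of unsolicited events and the expectedness reference all cover both agents, and the pause section itself opens by naming azithromycin. On this view two definitions and two instructions were simply not updated when Group D was written in. That is probably how it happened, and it rules out one tempting inference, that the protocol deliberately excludes azithromycin from its safety rules. It does not repair the rule. In the pause section azithromycin is named only to explain why there are no safety endpoints, and nothing there changes the definition of a SUSAR.

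A reader might also infer that a serious azithromycin reaction would go unreported. The documents do not support this. Under heading 115 every SAE goes to the sponsor and the local safety monitor within 24 hours, and to the regulator under its own requirements. All SAEs reach the ethics committee in the annual report, and deaths are reported for its next meeting.

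Nor can it be said that the SUSAR deadlines are simply lost. The ethics committee sentence carries its own description, by *study product*, and can be read without section 7.1.4. A separate provision sends new information that may alter the safety or conduct of the trial to the sponsor, the safety monitor, the ethics committee and the regulator, generally within 5 calendar days. That is shorter than 7 or 15, but it depends on someone deciding that the information qualifies. The regulator's deadlines are tied to the term SUSAR alone, so some doubt remains there.

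Finally, the 7 and 15 days are reporting deadlines. They do not measure a delay before pausing, and they cannot be turned into a count of further children dosed.

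**Conclusion.** The point holds as an internal inconsistency in a safety rule. On the literal definition, a serious unexpected azithromycin reaction in Group D does not trigger the only automatic pause, and in the 28 days before vaccination no other outcome is possible under that definition. The effect on the 7- and 15-day deadlines is uncertain rather than established.

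The size is small: 35 of 365 planned children, with SAE reporting intact. The conclusion assumes that section 7.1.4 is the governing definition and that *study product* is not defined elsewhere in the protocol; no definition appears in the text available. The matter is minor in reach but worth correcting, because the rule gives the wrong result if followed as written.

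**What to change.** - **Heading 105 and section 7.1.4, relatedness instructions:** replace *study vaccine(s)* with *study vaccine or azithromycin*.
- **Section 7.1.4, SAR and SUSAR definitions:** make the same replacement. Leave the sentence on solicited reactions in the week after Nasovac-S as it is; it is correctly vaccine-specific.
- **Heading 117:** state that a SUSAR to either agent pauses recruitment.
- **Heading 115:** define *study product* as either agent for reports to the ethics committee and the regulator. Limit the sentence on reporting to the Serum Institute of India to SUSARs related to Nasovac-S; otherwise the new definition would send azithromycin reactions to a company that does not make azithromycin.

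The cost is a few words in four places. No data collection, visit or sample size changes: azithromycin events are already collected through day 28, their relatedness is already classified, and an expectedness reference for both agents is already named.
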